#### Laboratory tests

A maternal whole blood sample obtained by venipuncture will be collected at study entry, monthly until delivery, at birth and at two postpartum visits (figure 2). Maternal HBV DNA, alanine aminotransferase (ALT) and creatinine will be measured at all scheduled visits for the mother. Serum phosphate will be measured at baseline and at birth.

#### Monthly visits during pregnancy

From the time TDF commences, the pregnant women will return for a monthly study visit. Obstetric follow-up at each monthly visit will include vital signs, weight, symphysis fundal height measurement and fetal heart beat and concomitant medications will be recorded into the case report form (CRF). Fetal growth will be measured monthly by ultrasound (head circumference, abdominal circumference and femur length).

Adverse events (AE) will be reviewed, and reported as AE or serious AE according to the problem. Compliance will be monitored by pill counting and a questionnaire on adherence.

#### Delivery

Pregnancy complications and mode of delivery will be recorded in the CRF. Anthropometric measurements of the infant will be done in the first hour of life and will include birth weight, length, head and arm circumference, by trained staff and according to standard operating procedures.

Vaccination: HBIG (if mother is HBeAg positive) and standard HBV vaccine (at birth and 2, 4 and 6 months of age) will be provided to the infants according to the Expanded Program on Immunization.^37–39^

At birth, a 12 mL sample of cord blood, 6 mL into EDTA and 6 mL into a plain tube will be collected for analysis of HBV DNA and tenofovir concentration and HBsAg reflecting the HBV status of the infant. Note this cord blood sample might not be collected if the woman is referred for caesarean section into the public hospital system.

A maternal serum sample will be used to measure ALT, creatinine, phosphorus, HBsAg (HBeAg only if the woman was HBeAg positive at baseline) and tenofovir concentration.

#### Postpartum follow-up

TDF will be continued until 1 month post partum to decrease the risk of flares as the maternal immune system returns to baseline. All women will continue the study until the 4 month postpartum visit. At the 1 and 4 months postpartum visits, ALT will be measured. If ALT concentrations are increased, but there is not a true flare, follow-up will continue and repeat ALT testing will be done at 6 months. If the flare worsens or does not resolve, they will be placed on anti-HBV therapy and be reviewed by a physician.

All infants will be followed at 1, 2, 4 and 6 months. The infant will be screened for HBV at 2 months. At each visit, infant anthropometry will be measured (body weight, length, head circumference) and feeding recorded. At 6 months, neurodevelopment will be assessed. At months 2, 4 and 6, the infant will receive follow-up HBV vaccinations.

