**Laboratory tests**							
HBsAg/HBeAg	X						
HBV DNA	X	X	X	X			
Creatinine	X	X	X	X			
Serum phosphate	X		X				
ALT	X	X	X	X		X*	
TDF concentration			X†				
Cord HBsAg/HBV DNA			X†				
Infant HBsAg					X‡		
Pill count		X	X	X			
Adverse event assessments		X	X	X			
Infant anthropometry			X	X	X	X	X
Infant neurodevelopment							X
Adherence survey		X	X	X			
Infant HB vaccination			X§		X	X	X

*Follow-up will continue if suspected or confirmed flare.

†Cord blood sample.

‡Venepuncture sample blood and only for hepatitis B surface antigen (HBsAg).

§If mother hepatitis B e antigen (HBeAg) positive also hepatitis B immunoglobulins (HBIG).

ALT, alanine aminotransferase; HBV, hepatitis B virus; PP, post partum; TDF, tenofovir disoproxil fumarate.

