#### Laboratory-based stopping criteria

ALT: monthly lab results will be compared with baseline. Grade 3 or higher elevations will be an indication to stop the drug; grade 3 or higher is >5× upper limit of normal (ULN) if baseline levels were below the ULN; or if baseline levels were >ULN, then grade 3 or higher is >3.5× the baseline value. The ULN of ALT will be defined as (0–31 U/L).^40^

Creatinine: a creatinine value of more than 1.0 mg/dL will be an indication to stop the drug regardless of the baseline value.^40^

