#### Hepatic flare

Although TDF is thought to be safe and acceptable in pregnancy, after discontinuation it might lead to hepatitis flares. There are conflicting data about the proportion and severity of flares after discontinuing antiviral therapy.^44–46^ There are no data in pregnant women regarding flares with longer duration of treatment and lower HBV DNA at delivery, nor is there information about predisposing characteristics to provide recommendations either before, or even after, flares start. We will determine the proportion of woman who have a moderate (ALT >2.5× ULN) or severe (ALT >5× ULN) hepatitis flare after discontinuation of TDF.^47^ We will estimate the impact of potential risk factors such as age, number of prior pregnancies and so on for moderate or severe flares by including treatment duration and HBV DNA concentration at study start and at delivery into multivariable regression models.

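### The flare outcome after stopping TDF is one ALT at 4 months post partum judged on ULN multiples alone: it misses episodes that have resolved and counts an unchanged ALT above 77.5 U/L as a flare

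*Protocol article*

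**What the plan says.** The Objectives list the rate of postpartum hepatic flares after TDF is stopped as a secondary objective. The Hepatic flare section states the outcome as a proportion: "We will determine the proportion of woman who have a moderate (ALT >2.5× ULN) or severe (ALT >5× ULN) hepatitis flare after discontinuation". The ULN, given under Laboratory-based stopping criteria, is 31 U/L.

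On timing, the Postpartum follow-up section says "TDF will be continued until 1 month post partum to decrease the risk of flares", and Table 2 marks the 1-month visit as the stop visit. The same section says "At the 1 and 4 months postpartum visits, ALT will be measured". Laboratory tests describes maternal blood draws as "monthly until delivery, at birth and at two postpartum visits", and the ALT row of Table 2 agrees: 1 and 4 months, nothing at 2 months.

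Anything later is conditional. "If ALT concentrations are increased, but there is not a true flare, follow-up will continue and repeat ALT testing will be done at 6 months". The Table 2 footnote to the 4-month ALT reads "Follow-up will continue if suspected or confirmed flare". Table 2 has a maternal physical examination at 4 months but no adverse-event assessment after 1 month.

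Two statements do not fit this schedule. Laboratory tests says "Maternal HBV DNA, alanine aminotransferase (ALT) and creatinine will be measured at all scheduled visits for the mother", yet Table 2 has no HBV DNA or creatinine at 4 months, the mother's last visit. The Abstract gives postpartum sampling at 1, 2, 4 and 6 months without saying whether mother or infant is meant.

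**The concern.** The outcome is worded as the share of women who have a flare after stopping, which a reader will take as cumulative over the off-treatment period. One blood sample at the end of that period cannot give this. An episode that begins and resolves between the 1-month and 4-month visits leaves no trace in the scheduled data.

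The cut-offs also make no use of the woman's own earlier ALT, although it is measured at baseline, monthly, at delivery and at 1 month. A woman whose ALT was already above the cut-off and has not moved is recorded as having a flare after discontinuation.

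The Background names flare after discontinuation as one of three main barriers to using TDF, and the Hepatic flare section says there are no data for longer treatment in pregnancy. A low figure could be read as reassurance about stopping. The planned risk-factor models would inherit both kinds of misclassification.

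**Working it through.** **The plan's own figure.** The only calculated figure in the article is the sample size for the proportion undetectable at delivery: 1.96² × 0.5 × 0.5 / 0.08² = 150.06, which reproduces the stated 150. It was not derived for flare, and the article gives no flare frequency, onset or duration.

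**Off-treatment ALT values per woman.** TDF ends at 1 month. ALT is scheduled at 1 month (on treatment) and at 4 months (off treatment). That leaves one scheduled off-treatment value, 3 months or 3 × 365.25 / (12 × 7) = 13.04 weeks after stopping. The 6-month repeat needs an ALT that is already raised, so it cannot recover an episode that has resolved by 4 months.

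**Share of episodes seen (assumed onset and duration).** Let ALT stay above the cut-off for D weeks. An episode is seen only if a sample falls within it.

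- Set-up A: onset uniform over the full 13.04 weeks, sample at 13.04. Share seen = D / 13.04.
- Set-up B: onset uniform over weeks 0 to 12, sample at week 13. Share seen = (D − 1) / 12.

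| D (weeks) | A: 4-month ALT only | B: 4-month ALT only | A: with a 2-month ALT | B: with a 2-month ALT |
|---|---|---|---|---|
| 4 | 31% | 25% | 61% | 58% |
| 6 | 46% | 42% | 79% | 78% |
| 8 | 61% | 58% | 95% | 94% |
| 12 | 92% | 92% | 100% | 100% |

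The result depends on the onset assumed. Under B, an episode is seen only if it begins at or after week 13 − D. With onset between weeks 8 and 12, a 4-week episode is seen (12 − 9) / 4 = 75% of the time and a 6-week episode always. A 4-week episode that begins before week 9 is never seen.

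**Illustration.** Suppose 10% of 150 women, that is 15, truly have a flare. At 25% to 61% detection, about 4 to 9 are seen. The Hepatic flare section names at least five covariates for its models (age, prior pregnancies, treatment duration, HBV DNA at start and at delivery).

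**Definition.** The cut-offs are 2.5 × 31 = 77.5 U/L and 5 × 31 = 155 U/L. Table 1 has no ALT criterion, and the stopping criteria expressly provide for baselines above the ULN. ALT unchanged throughout at 90 U/L (90 / 31 = 2.9 × ULN) is a moderate flare under this definition, and unchanged at 160 U/L (5.2 × ULN) a severe one. ALT unchanged at 32 to 77 U/L is raised but is not counted.

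**Net direction.** Take a true 10% with D = 6 under set-up A: 4.6% is seen. If 2% of women are stably above 77.5 U/L, the reported figure is 6.6%; if 5%, it is 9.6%. With D = 8 and 5% stable, it is 6.1% + 5% = 11.1%, above the truth. The 2% and 5% are assumptions, since the article gives no ALT distribution.

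**The case against.** Several counter-arguments have force.

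- **The detection figures are scenario-dependent.** This stands. They show that the design cannot say what share it captures; they do not estimate that share. A reader might infer that the flare proportion will be too low. The documents do not support that, because the definition pushes the other way.
- **Only some stable ALT is misclassified.** This stands. A reader might infer that any stable raised ALT counts as a flare; it counts only above 77.5 U/L, and the number of such women is unknown.
- **The stopping criteria and the flare definition do not conflict.** It is tempting to set the stopping rule ("or if baseline levels were >ULN, then grade 3 or higher is >3.5× the baseline value") against the ULN-only flare cut-offs and call this a contradiction. It is not one. The first governs stopping drug during treatment; the second classifies an outcome after treatment. They need not share a reference value.
- **The missing 4-month HBV DNA.** One might infer that an ALT rise could not be linked to viral rebound. That presumes Table 2 prevails over the text, and no planned analysis makes the link. What remains is a mismatch within the article.
- **The Abstract may imply sampling at 2 months.** If that meant the mother, much of the timing concern would go. But Laboratory tests, Postpartum follow-up and Table 2 agree on maternal ALT at 1 and 4 months only.
- **Flares with symptoms may come to notice between visits.** Possible, but Table 2 schedules no adverse-event assessment after 1 month, so this is not systematic.
- **Flare is a secondary, descriptive outcome.** True, and it limits the weight of the point.

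**Conclusion.** The point holds in a limited form. Every woman has one scheduled off-treatment ALT, so the planned flare proportion is a point prevalence about 3 months after stopping. Under uniform onset, about 25% to 61% of episodes lasting 4 to 8 weeks would be seen. The share nears 100% for long or late episodes and falls to zero for short early ones. These figures rest on assumed onset and duration; that resolved episodes go uncounted does not.

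Separately, a woman whose ALT is stably above 77.5 U/L is recorded as having a flare after discontinuation. The two errors run in opposite directions and neither can be sized from the article, so the net bias is unknown. The schedule matters most, because no later analysis can recover ALT values that were never measured.

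**What to change.** These changes concern the analysis outcome and its description, not the management of any woman.

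1. **Definition.** Count a post-cessation flare only when the 4-month ALT exceeds the stated ULN multiple and has risen from the woman's 1-month, end-of-treatment ALT by an amount fixed in advance. At minimum, she was not already above that same cut-off at 1 month. The investigators choose the amount. Report the ULN-only proportion as a sensitivity analysis. Cost: wording only, since the 1-month ALT is already collected.
2. **Label.** Describe the result as the proportion with raised ALT 3 months after stopping, not as a rate or cumulative proportion of flares. Cost: wording only. The alternative is to add a maternal ALT for the outcome when the infant is seen at 2 months. In the scenarios above, that raises the share of 4- to 8-week episodes seen to about 58% to 95%. It is not free: Table 2 lists only infant procedures at that visit, so the mother's attendance is inferred. It needs one extra maternal blood draw (150 to 170 in all) and an amendment through the approving committees.
3. **Consistency.** Reconcile Laboratory tests with Table 2 on HBV DNA and creatinine at 4 months, and the Abstract with Laboratory tests and Postpartum follow-up on sampling times, stating which samples are the mother's. Cost: wording only, unless the reconciliation adds a test.

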#### Laboratory-based stopping criteria

ALT: monthly lab results will be compared with baseline. Grade 3 or higher elevations will be an indication to stop the drug; grade 3 or higher is >5× upper limit of normal (ULN) if baseline levels were below the ULN; or if baseline levels were >ULN, then grade 3 or higher is >3.5× the baseline value. The ULN of ALT will be defined as (0–31 U/L).^40^

Creatinine: a creatinine value of more than 1.0 mg/dL will be an indication to stop the drug regardless of the baseline value.^40^

#### Sample size

We calculated the sample size required to estimate the proportion of pregnant women expected to be undetectable at delivery with precision.

$$n=\frac{{\left(1.96\right)}^{2}p\left(1-p\right)}{d^{2}}$$

There is no prior knowledge to predict the proportion of pregnant women expected to be undetectable at delivery, so we used the most conservative estimate. When this proportion is 50%, the required sample size is the largest. Based on a 95% CI, a margin of error d=8% and a conservative estimation of proportion p=0.5, a sample size of n=150 is required. We aim for n=170 to allow for attrition.

### Data analyses

#### HBV viral kinetics

The Kaplan-Meier method will be used to estimate the median time from initiation of TDF to an HBV DNA <100 IU/mL including all women and then, based on the distribution of HBV DNA, stratified by high versus low HBV DNA groups. We expect those with low HBV DNA at enrolment to have <100 IU/mL at the time of delivery, but it is important to include them in this study to calculate the trajectory of decline and determine how long they need to be treated to reach HBV DNA <100 IU/mL. A generalised estimating equation model will be used to assess whether baseline HBV DNA and adherence to TDF are associated with the logarithmically transformed HBV DNA over time. A proportional hazard model will be constructed to assess the HR of reaching undetectable HBV DNA adjusting for the baseline HBV DNA concentration and adherence to TDF (# pills actually taken/# pills that should have been taken). For missing HBV DNA data, depending on the reasons for being missing, imputations using multiple imputations by chained equations will be used. Sensitivity analyses will then be performed comparing analyses using complete and imputed data sets. The proportion of women with undetectable HBV DNA at delivery will be reported with 95% CI in all women and by high versus low HBV DNA groups. Median and IQR of HBV DNA at baseline and each visit will be reported. Then, HBV DNA will be logarithmically transformed and the median HBV DNA at baseline and at delivery will be compared using paired t-tests. Additional analyses may be conducted to further explore the data.

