The usage of antivirals for HIV in limited-resource settings has shown remarkable scale up and success and is a vital component of antenatal care (ANC) programmes.^8^ Antivirals that are active against HBV like tenofovir disoproxil fumarate (TDF) may reduce the risk of MTCT by reducing the HBV DNA across gestation to a minimum at the time of delivery when MTCT typically occurs and might be a more feasible option than HBIG in a limited-resource setting.^9^ The optimal gestational age to commence TDF is critical to know to ensure HBV DNA is as low as possible prior to birth.^10^ The precise threshold of HBV DNA, in the absence of HBIG that prevents MTCT, is also still unknown. Initially, an HBV DNA of ≥6 log10 IU/ml was associated with a higher risk of MTCT, suggesting that women in this category were the most important to target for antiviral therapy.^11–13^ Although a maternal HBV DNA <6 log10 IU/ml is thought to be lower risk for MTCT, the studies reporting this provided the infants with HBIG and vaccination. Although provision of TDF 300 mg daily in the third trimester of pregnancy significantly reduced perinatal transmission (OR 0.10; 95% CI 0.01 to 0.77; p=0.03),^6 14–16^ a mean of 8.6±0.5 weeks of TDF prior to delivery resulted in a mean HBV DNA at delivery of 4 log 10 IU/mL with 32% of mothers having HBV DNA >5.3 log 10 (or 200 000 IU/ml).^6^ This amount of HBV DNA is too high to forego HBIG, and if provided, may still not be sufficient to prevent infection. In the same study, HBV DNA declined another log (median 3.52 log10 IU/ml) in the 4 weeks post partum that TDF was provided. Gao *et al* showed that starting TDF treatment at an estimated gestational age of 24–27 weeks may achieve better suppression compared with starting in third trimester.^16^

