Existing data from trials involving non-pregnant patients are not informative due to differences in age, stage of HBV, frequency of HBV DNA testing and immune response and pharmacokinetics of TDF in pregnant women compared with non-pregnant patients.^17–20^ Pharmacokinetic studies have established that the area under the curve and maximum drug concentration (C_max_) of TDF are decreased in the second and third trimester of pregnancy, and clearance is increased.^18 21–24^ In a systematic review of TDF pharmacokinetics in pregnancy, none of the manuscripts reported reaching the TDF C_max_ of 300 ng/mL the efficacy threshold determined in non-pregnant HBV infected women.^23^ These data suggest that TDF dosage and treatment initiation that are accurate for HIV and non-pregnant HBV-infected patients may not be accurate for pregnant HBV-infected women.

While some of the safety issues have been resolved with the use of TDF for prevention of MTCT of HIV, gaps remain regarding HBV.^25 26^ The main barriers to implementation of TDF are a (1) lack of knowledge by the women of hepatitis B, of their infection status, and of prevention strategies,^27^ (2) poor adherence to the prophylactic drug regimen,^9^ and (3) potential for hepatitis flares after postpartum drug discontinuation.^28^ All of these need to be evaluated and addressed in limited-resource settings where HBV is highly endemic.^29^

The aim of this prospective interventional study is to determine the appropriate time in pregnancy to initiate TDF treatment of HBV in order to reach HBV DNA <100 IU/mL at delivery. Knowing this will allow future studies where TDF can be initiated at the appropriate time so that HBIG may not be needed to prevent MTCT of HBV. The viral kinetics of HBV DNA in pregnant women receiving daily oral TDF commenced before 20 weeks gestation will be measured monthly. Infants will receive HBIG and birth-dose monovalent HBV vaccine. MTCT will be assessed at 2 months post partum. While the study population is pregnant women attending antenatal and birth services on the Myanmar–Thailand border, the study has worldwide application to women who are pregnant and HBV positive. Moreover, we will study safety, feasibility and potential barriers to implementation of TDF in routine ANC in a limited-resource setting.

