### Objectives

The primary objective is to estimate the time to HBV DNA suppression <2 log10 IU/mL (or <100 IU/mL) in HBV DNA positive women who start TDF late in the first or early in the second trimester.

Secondary objectives include: estimation of the proportion of women with HBV DNA <2 log10 IU/mL (or <100 IU/mL) at delivery; the concentration of TDF in maternal and cord blood at birth in women who have detectable HBV DNA and a subset of women with undetectable HBV DNA; to monitor the safety of TDF on the Myanmar–Thailand border in pregnant women with low health literacy rates^30^ and address potential barriers to implementing TDF in early pregnancy to prevent MTCT of HBV; to determine the rate of hepatic flares post partum after cessation of TDF; to estimate the proportion of cases of vertical transmission in infants of 2 months of age; to assess fetal growth by monthly ultrasound, and infant growth at 1, 2, 4 and 6 months and neurodevelopment at 6 months.

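### Time to HBV DNA <100 IU/mL is summarised only by medians, overall and by a data-driven high/low split, but the start-time aim needs the time by which most women are suppressed

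*Protocol article*

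**What the plan says.** Background and rationale gives the aim: to "determine the appropriate time in pregnancy to initiate TDF treatment of HBV in order to reach HBV DNA <100 IU/mL at delivery". The Objectives section puts it as follows: "The primary objective is to estimate the time to HBV DNA suppression <2 log10 IU/mL (or <100 IU/mL) in HBV DNA positive women". The population there is women whose treatment begins around the end of the first trimester or the beginning of the second, and no summary measure is named.

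Data analyses, HBV viral kinetics, supplies the measure: "The Kaplan-Meier method will be used to estimate the median time from initiation of TDF to an HBV DNA <100 IU/mL including all women". A second estimate follows in the same sentence, split into a high and a low HBV DNA group formed from the observed distribution. On the low group the section remarks: "We expect those with low HBV DNA at enrolment to have <100 IU/mL at the time of delivery". It also plans:
- a generalised estimating equation model of log HBV DNA over time;
- a proportional hazards model adjusted for baseline HBV DNA and adherence;
- the proportion undetectable at delivery with 95% CI, overall and by high/low group.

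No upper percentile of time to suppression is named, and no target proportion suppressed. The value of the high/low cut is not stated, and gestational age at TDF start is not among the named covariates.

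**The concern.** The aim asks how long before delivery treatment must begin for women to be suppressed when they deliver. That is a question about the upper part of the distribution of time to suppression, where the slower women lie. The median describes the middle. Stratifying does not change this, because each stratum median still leaves half of that stratum at or above 100 IU/mL.

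The overall median has a second weakness. It mixes in low-DNA women, whom the plan already expects to be suppressed by delivery, and they shorten it. Setting the high/low cut after seeing the distribution leaves the stratum results open to choice.

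Background and rationale says the answer should let future studies start TDF at a time that may make HBIG unnecessary. If the reported medians are taken as the answer, the time that slower women need would be understated.

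**Working it through.** **1. The plan's own figure.** Sample size uses n = 1.96² × p(1−p)/d² with p = 0.5 and d = 0.08: 3.8416 × 0.25 / 0.0064 = 150.06. The stated 150 reproduces. This figure concerns the proportion undetectable at delivery, not any percentile of time.

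**2. What the plan expects at delivery.** The Adherence section anticipates 10–15 women detectable at delivery.
- Of 170: 10/170 = 5.9% to 15/170 = 8.8%.
- Of 150: 10/150 = 6.7% to 15/150 = 10.0%.

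So roughly 90–94% suppression is expected, against 50% at a median.

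**3. Distance between the median and the 90th percentile.** The document gives no time-to-suppression figures, so this is an illustration. Assumptions: Weibull times with shape k from 1 to 2; delivery at 40 weeks, so starts at 12 to <20 weeks give about 20–28 weeks on TDF; 90–94% suppressed by then.

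The time by which a proportion p is suppressed is scale × (−ln(1−p))^(1/k). The ratio of median to 90th percentile is therefore (ln 2/ln 10)^(1/k) = 0.301^(1/k):

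| k | median / 90th percentile |
|---|---|
| 1 | 0.30 |
| 1.5 | 0.45 |
| 2 | 0.55 |

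Example: 90% suppressed at 24 weeks with k = 1.5 gives a median of 24 × 0.45 = 10.8 weeks. Over all combinations the median runs from 4.9 to 15.4 weeks and the 90th percentile from 16.4 to 28.0 weeks.

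**4. Effect of pooling.** Assumptions: high-DNA share h of 0.327, 0.5 or 0.6; low/high stratum medians of 4/12, 4/16 or 6/16 weeks; k = 1.5. In each stratum with median m, F(t) = 1 − exp(−ln 2 × (t/m)^1.5). The pooled median solves h·F_high(t) + (1−h)·F_low(t) = 0.5.

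Example: h = 0.327 with medians 4 and 12 gives t = 5.3 weeks. There F_high = 0.18 and F_low = 0.65, and 0.327 × 0.18 + 0.673 × 0.65 = 0.50.

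Over all nine combinations:

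| Quantity | Range |
|---|---|
| Pooled median | 5.3–10.4 weeks |
| High group suppressed at that time | 13–30% |
| Low group suppressed at that time | 64–89% |
| High group's 90th percentile | 26.7–35.6 weeks |

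In addition, HBeAg-negative women qualify at HBV DNA >85 IU/mL, so any enrolled at 86–99 IU/mL are below the event threshold at time zero. They too shorten the pooled median.

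**5. Is the 90th percentile reachable?** Suppose all 10–15 detectable women are high-DNA.
- If 32.7% of 170 are high (about 56), 41/56 = 73% to 46/56 = 82% of them are suppressed by delivery.
- If half are high (85), 70/85 = 82% to 75/85 = 88% are.

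On that assumption the 90th percentile is not reached by delivery in the high group. The cumulative proportion at set weeks can be estimated either way.

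**The case against.** The strongest reply is that the planned analyses already hold most of the answer. A Kaplan-Meier curve yields every percentile reached during follow-up. The proportion suppressed at delivery is reported by DNA group, and the hazard model adjusts for baseline HBV DNA. A median is also a conventional summary of time to an event, and an analysis plan not shown here may tabulate further percentiles.

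Much of this stands, and it rules out several stronger readings that a reader might infer:
- **That the analysis only pools.** It does not; the same sentence goes on to "based on the distribution of HBV DNA, stratified by high versus low HBV DNA groups".
- **That the trial cannot answer its question.** The curves and the proportion at delivery carry relevant information. What is missing is a commitment to the part of the curve that answers it.
- **That the plan would set the start one median before delivery and so fail half the women.** No section states such a rule.
- **That 5.3 log10 is the plan's own cut.** The figure behind "32% of mothers having HBV DNA >5.3 log 10" is a level at delivery in a cited study, after a mean of 8.6 weeks of TDF. The same section also mentions 6 log10. Neither is set as a baseline stratum.
- **That about 67% of the sample is low-DNA because HBeAg prevalence is 32.7%.** That prevalence is among all HBsAg-positive women. Table 1 excludes HBeAg-negative women without HBV DNA, so the enrolled HBeAg-positive share should be higher. HBeAg status is also not the same as DNA group.

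Two parts of the reply do not settle the matter. The proportion suppressed at delivery describes women who started at 12 to <20 weeks; it shows whether that window sufficed, not how much treatment time was needed. And the article does name a summary for time to suppression, so the mismatch with the aim is in the text itself.

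**Conclusion.** The point holds as a mismatch between the aim and the named summary. Medians, overall and by stratum, do not give the time by which most women are suppressed, and no other summary of time to suppression is fixed. That half are unsuppressed at a median is true by definition and needs no assumption. The contrast with the 10–15 detectable women anticipated at delivery comes from the document.

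The size of the gap is illustrative only: the median is 30–55% of the 90th percentile under the Weibull shapes used, and 13–30% of high-DNA women are suppressed at the pooled median under the assumed shares and stratum medians. These figures show direction and plausible scale and do not measure an error in this trial. The unfixed high/low cut and the absent covariate for gestational age at start are lesser parts of the same point. The design, the data collection and the sample size arithmetic are not called into question.

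**What to change.** In Data analyses, HBV viral kinetics:
1. Base the start-time conclusion on two readings of the same Kaplan-Meier curves: the cumulative proportion below 100 IU/mL at set weeks on TDF, and the 90th percentile of time to suppression. Give each a 95% CI, and report the percentile as not reached where that applies.
2. Report both by baseline HBV DNA groups, with the cut stated and justified before analysis.
3. Keep the overall and stratum medians as descriptive results.
4. Add gestational age at TDF start to the proportional hazards model, since Background and rationale reports lower tenofovir exposure in the second and third trimesters. State that the data do not directly support conclusions about starts outside the observed 12 to <20 weeks.

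The cost is wording only. Monthly HBV DNA up to delivery, and again at 1 month post partum, is already in Table 2. The price is precision: upper percentiles have wider intervals than medians and may not be reached in the high-DNA group. This is why the cumulative proportions should stand beside them.
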